The sensation of fatigue may be independent from objective measures of performance (Bailey et al., 2007; Krupp & Elkins, 2000; Lou et al., 2003). For example, Fietsam et al. (2023) found that individuals with long COVID reported more fatigue than individuals without long COVID but had similar levels of performance decline on an isokinetic fatigue task. The decline in an objective measure of performance over a discrete period of time is termed performance fatigability (Enoka et al., 2021). Understanding the association between fatigue and fatigability has been identified as an important goal for clinical research (Kluger et al., 2013). We will address this in our second research question by quantifying whether the change in performance over the cognitive and physical tasks (performance fatigability) is related to state fatigue induced by that task, whether this moderates the relation between somatosensory processing and state fatigue, and whether this is impacted by long COVID (Research Question 2).

In addition to understanding if somatosensory processing predicts fatigue, it is also of relevance to ask if fatigue impacts somatosensory processing (bidirectional arrows in Figure 1, blue boxes). This would potentially indicate that activities that increase fatigue and cause performance fatigability, could lead to disrupted somatosensory processing, further increasing the fatigue and fatigability. This will be addressed in our third research question, where we ask if the change in somatosensory attenuation (Research Question 3i) and somatosensory gating (Research Question 3ii) from pre‐ to post‐task is predicted by the change in state fatigue from pre to post task, fatigability during the task, population (long COVID/controls) and task (cognitive/physical).

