**FIGURE 2 eph13615-fig-0002:**
[figure not shown]
Data collection timeline. HRV, heart rate variability. JISC is a digital platform designed specifically for education and research organizations that can be used for the creation and dissemination of surveys. BL, baseline; PRE‐1, immediately after pre‐task somatosensory gating measure; PRE‐2, immediately after pre‐task somatosensory attenuation measure; POST‐1, immediately after the completion of the task (cognitive or physical); POST‐2, immediately after post‐task somatosensory gating measure; POST‐3, immediately after post‐task somatosensory attenuation measure.

On completion of the participant characteristics and validated measures, participants will be given a unique, randomly generated four‐digit identifier. Consent forms, which will contain the participants personal details, will be saved separately from all other data and only identified with the participants four‐digit identifier.

The protocol is split into two testing sessions. Each session is expected to take up to 90 min. The two sessions are identical, except that in one session participants perform a cognitive task and in the other session they perform a physical task. Participants will be asked to complete both sessions in a crossover design. In each session, somatosensory processing (attenuation and gating) will be measured pre‐ and post‐task (physical or cognitive). The order of the two sessions will be randomized using the command randi([1 2]) in MATLAB software version 23.2 (MathWorks Inc., Natick, MA, USA), which will be run on the morning of the first testing session. A value of ‘1’ indicates that cognitive task will be performed first and ‘2’ indicates that the physical task will be performed first. Participants will be asked to return on a separate day for each session.

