Hypothesis 2: State fatigue following exertion will be predicted by somatosensory attenuation at baseline, somatosensory gating at baseline, the presence of long COVID (long covid/controls), and the type of task (cognitive/physical). Performance fatigability will be considered a moderator variable in these relations. State fatigue prior to exertion will be included as a covariate in this analysis.

This will be tested using a linear mixed model:

$$Y_{ijk}=\mu +a_{i}+b_{j}+c_{k}+d_{ik}+e_{ik}+f_{ik}+g_{ijk}+\left(f_{ik}\times a_{i}\right)+\left(f_{ik}\times b_{j}\right)+\varepsilon_{ijk}$$
where:

*Y_ijk_
*: state fatigue following exertion in the *i*‐th group (long COVID/control) during task *j* (cognitive/physical) for the *k*‐th subject.μ: the overall mean of state fatigue following exertion.
*a_i_
*: the effect of the *i*‐th group (fixed effect: long COVID vs. control).
*b_j_
*: the effect of the *j*‐th task (fixed effect: cognitive vs. physical).
*d_ik_
*: the baseline somatosensory attenuation for the *k*‐th subject in the *i*‐th group.
*e_ik_
*: the baseline somatosensory gating for the *k*‐th subject in the *i‐*th group.
*f_ijk_
*: the performance fatigability for the *k*‐th subject in the *i*‐th group during the *j*‐th task.
*g_ijk_
*: the state fatigue prior to exertion for the *k*‐th subject in the *i*‐th group during the *j*‐th task (covariate).(*f_ik_
*×*a_i_
*): the interaction term between performance fatigability and group.(*f_ik_
*×*b_j_
*): the interaction term between performance fatigability and task.
*ϵ_ijk_
*: the residual error term, assumed to be normally distributed.
Hypothesis 3: The change in somatosensory attenuation (Research Question 3a) and somatosensory gating (Research Question 3b) from pre‐ to post‐task will be predicted by the change in state fatigue from pre to post, fatigability, the presence of long COVID (long COVID/controls), and the type of task (cognitive/physical).

We will use linear mixed models to test these hypotheses, with separate models for somatosensory attenuation and somatosensory gating:

$$Y_{ijk}=a_{i}+b_{j}+c_{ijk}+d_{ijk}+u_{0i}+\varepsilon_{ijk}$$
where:

*Y_ijk_
*: attenuation or gating at baseline in the *i*‐th group (long COVID/control) during task j (cognitive/physical) for the k‐th subject.
*a_i_
*: the fixed effect of the *i*‐th group (long COVID vs. control) on baseline attenuation.
*b_j_
*: the fixed effect of the *j*‐th task (cognitive vs. physical) on baseline attenuation.
*c_ijk_

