*: the change in state fatigue from pre to post in the *i*‐th group, during task *j*, for the k‐th subject, affecting baseline attenuation.
*d_ijk_
*: the change in fatigability in the *i*‐th group, during task *j*, for the *k*‐th subject,
*u*
_0_
*
_i_
*: random intercept for group *i*, capturing group‐level variability
*ϵ_ijk_
*: residual error term, representing random variability and measurement error not explained by the fixed effects.
Hypothesis 4: Among individuals with long COVID, trait fatigue will be effected by mood, illness beliefs, autonomic symptoms, increase in state fatigue induced by a physical task, the increase in state fatigue induced by a cognitive task, and autonomic nervous system function.

This will be tested using a linear mixed effects model:

$$Y_{i}=\mu +a_{i}+b_{i}+c_{i}+d_{i}+e_{i}+f_{i}+u_{0i}+\varepsilon_{i}$$
where:

*Y_i_
*: trait fatigue for individual *i*.μ: the overall mean of state fatigue following exertion.
*a_i_
*: mood for individual *i*.
*b_i_
*: illness beliefs for individual *i*.
*c_i_
*: autonomic symptoms for individual *i*.
*d_i_
*: change in state fatigue induced by physical task for individual *i*.
*e_i_
*: change in state fatigue induced by cognitive task for individual *i*.
*f_i_
*: autonomic nervous system function for individual *i*

*u*
_0_
*
_i_
*: random intercept capturing individual‐specific variability in trait fatigue not explained by the fixed effects.
*ϵ_i_
*: residual error term representing random variability and measurement error.

We will check the following assumptions of the regression models: linearity, independence, homoscedasticity, normality and multicollinearity.

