### Sample size

3.8

The study is powered to address Research Question 1a. Previous research indicates an effect size of 0.78 for differences in somatosensory attenuation between young and older individuals (Parthasharathy et al., 2022). Powering the current study to detect an effect size of 0.78 between two independent means for Research Question 1a—somatosensory attenuation in individuals with and without long COVID—with an α error probability of 0.05 and a power of 95% and based on a non‐directional two‐tailed hypothesis requires 44 participants per group (G*power 3.1.9.7). Dropout is not expected to impact Research Question 1a or 1b, as it involves initial measurements during the first session. However, there is a potential for dropout to impact the subsequent research questions, which rely on participants returning for a second session.

The sample size gives us power of 90% to detect an effect of 0.70 between two groups at two repeated time points with alpha error probability of 0.05 for Research Questions 2 and 3, or a power of 80% to detect an effect of 0.60. A dropout rate of 10% would mean that our power to detect these effect sizes decreases to 60%. The approach for addressing Research Questions 2 and 3 ensures that the study is adequately powered to detect correlations of 0.50 and 0.40, respectively. The code used to calculate the outcome measure is available at https://github.com/smancuso/R‐ Code/blob/cc90c623c4dc733fe5c93ef5a795dde010152c63/Power.R

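### Hypothesis 3 gives the session's fatigue change a single coefficient, which mixes between-person responsiveness with the within-person relation and cannot by itself show that fatigue alters somatosensory processing

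*Protocol article*

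**What the plan says.** The Introduction gives Research Question 3 a direction: "it is also of relevance to ask if fatigue impacts somatosensory processing". It adds: "This would potentially indicate that activities that increase fatigue and cause performance fatigability, could lead to disrupted somatosensory processing". Figure 1's caption proposes a bidirectional relation.

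The design supplies two sessions per person (Section 3.3): "Participants will be asked to complete both sessions in a crossover design".

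The Hypothesis 3 wording (Section 3.7) is that the change in processing "will be predicted by the change in state fatigue from pre to post, fatigability, the presence of long COVID" and task. The equation is Y_ijk = a_i + b_j + c_ijk + d_ijk + u_0i + ε_ijk. Three items in its legend matter here:

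- c_ijk is "the change in state fatigue from pre to post in the" given group, task and subject. It appears once, with no person mean and no deviation from that mean.
- u_0i is an intercept for group, "capturing group‐level variability". Group is already a fixed effect (a_i), so the two are aliased, and no term links a participant's two sessions.
- Y is "attenuation or gating at baseline in the" the given group and task. This conflicts with the hypothesis, which concerns the pre-to-post change.

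The exploratory reruns (Section 3.7.1) add age, time of day and session order. None of these separates the two sources of variation in c_ijk.

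**The concern.** A predictor that varies both between people and between a person's own sessions carries two relations. One slope is a weighted mix of them. If some people respond more to any exertion, in both rated fatigue and processing, the slope is non-zero even when a larger fatigue rise does nothing further to that person's processing. A significant coefficient could then be read as support for the fatigue-to-processing arrow in Figure 1 when it reflects only stable differences in responsiveness. The crossover contains information that would separate the two, and the printed model does not use it.

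**Working it through.** **The plan's own figure.** Section 3.8 gives 44 per group for Research Question 1a: "Powering the current study to detect an effect size of 0.78 between two independent means", two-sided 0.05, power 95%. The exact noncentral t gives power 0.947 at 43 and 0.951 at 44, so 44 reproduces. No figure is stated for the Hypothesis 3 slope.

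**Inputs.** From the article: 44 per group (88 people), two sessions each, group and task as fixed effects. Assumed, because the article gives neither: ICC, the share of variance that is stable between people, set equal for fatigue change and processing change; and r, the correlation of the stable person-level parts within group. Both variables have unit variance. The true within-person slope b_W is 0 unless stated. The fatigability term was left out of the simulation.

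**Step 1: what the printed model estimates.** With the group intercept aliased, the fit is ordinary least squares and the expected slope is ICC × r + (1 − ICC) × b_W.

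- ICC 0.3, r 0.3: 0.3 × 0.3 = 0.09 (simulated 0.089).
- ICC 0.5, r 0.5: 0.5 × 0.5 = 0.25 (simulated 0.247).
- The sign can reverse. With ICC 0.6, r = −0.7 and b_W = +0.30: 0.6 × (−0.7) + 0.4 × 0.30 = −0.42 + 0.12 = −0.30 (simulated −0.296).

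The first case checks against theory. The standard error is about √((1 − 0.09²)/172) = 0.076, and 0.09/0.076 ≈ 1.18, so rejection should be near 22%. Simulation gives 23%.

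**Step 2: a subject intercept alone.** With two sessions and equal ICCs, generalised least squares weights the between-person and within-person slopes about equally. The slope of person means is 2 × r × ICC/(1 + ICC), so with b_W = 0 the mixed slope is about r × ICC/(1 + ICC). For ICC 0.3 and r 0.3 this is 0.09/1.3 = 0.069 (simulated 0.069). The bias shrinks but stays.

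**Step 3: false rejection at 0.05, b_W = 0, 2,000 runs per scenario.** Ranges show repeat runs.

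| r | ICC | Printed group intercept | Subject intercept, one slope |
|---|---|---|---|
| 0.3 | 0.3 | 23% | 15–16% |
| 0.3 | 0.5 | 50–53% | 27–30% |
| 0.3 | 0.7 | 74–75% | 37–42% |
| 0.5 | 0.3 | 52% | 34–37% |
| 0.5 | 0.5 | 90% | 65% |
| 0.5 | 0.7 | 99% | 83–86% |

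The test on between-session differences rejects 4.5% to 6.0% throughout. At ICC 0.1 with r up to 0.3, the single coefficient rejects about 5% to 8%. With r = 0 the printed model still rejects 6% to 12%, because it ignores that sessions are paired within people.

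**Step 4: splitting the term without changing the random effect.** With the mean and deviation terms added to the printed group-intercept model at r = 0.3, the deviation test rejects about 2%, 1% and 0.1% under the null at ICC 0.3, 0.5 and 0.7. Its power at a within-person correlation of 0.30 is about 72%, 56% and 27%. The subject intercept must be part of the fix.

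**Step 5: power of the separated test.** By Fisher z with 88 people, (1.96 + 0.84)/√85 = 0.304, a correlation of about 0.30 at 80% power. With 79 people (10% dropout), 2.80/√76 = 0.321, about 0.31. Section 3.8 names 0.40 for Research Question 3, although that may be a different metric.

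**The case against.** - **Each session already uses the person as their own control.** This stands. Under the hypothesis wording, both outcome and predictor are pre-to-post changes, so stable levels of fatigue, severity or force matching cancel. A reader might infer that any trait-level correlation would produce the coefficient. The hypothesis does not support that. It would follow only from the legend's baseline definition of Y, which contradicts the hypothesis.
- **The research question asks only about prediction.** This partly stands. A between-person association answers a predictive question, and the Introduction's causal wording is hedged. The point therefore concerns the directional reading, not the fitting of the model.
- **The within-person slope has its own limits.** This stands. With two sessions it rests on one cognitive-versus-physical contrast. Someone who responds strongly but equally to both tasks adds nothing to the slope. A common slope is assumed although the Introduction says it is unclear whether fatigue dimensions share mechanisms.
- **The size rests on assumed inputs.** This stands. At low ICC the problem nearly vanishes.
- **An article may leave such refinements to a fuller plan.** This does not answer the point, because the equation is printed in full with one term and a group intercept.

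A reader might also extend the point to pre-exertion fatigue in Hypothesis 2. There it is only an adjustment covariate, and no harm has been shown.

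**Conclusion.** As printed, the Hypothesis 3 fatigue-change coefficient cannot by itself support the statement that fatigue impacts somatosensory processing. That much follows from the equation and the two-session design. The size does not. At an assumed r of 0.3 and ICC of 0.3 to 0.7, false rejection is about 15% to 40% with a subject intercept and 23% to 75% with the printed group intercept, and it is near nominal at ICC 0.1. The documents do not show that such confounding is present. With Y as the change, it is limited to stable responsiveness, and the group term already removes the between-group part. Research Question 3 is not the question the study is sized for, but Section 3.9 announces a Stage 2 registered report, so the prespecified model matters.

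**What to change.** For Hypothesis 3 only:

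1. Define Y as the pre-to-post change in attenuation or gating, so that legend and hypothesis agree.
2. Replace the group random intercept by a subject random intercept.
3. Replace c_ijk by two terms: the participant's mean fatigue change over the two sessions, and the session's deviation from that mean. Fatigability may be split the same way, once it is on a common scale across tasks (Section 3.4 uses the balanced integration score for one and walking speed in m/s for the other).
4. Report both coefficients. Rest any statement that fatigue alters processing on the within-person one, and describe the between-person one as association.

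The cost is two derived variables and one extra fixed effect per model, with no new data. The within-person coefficient is less precise (80% power at a correlation of about 0.30 with 88 people), assumes one slope for both tasks, and draws nothing from people who respond equally to both. It also remains observational, because fatigue change is not randomised.

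### The Hypothesis 3 models omit each session's pre-task attenuation or gating, so the cognitive versus physical task contrast is less precise than the collected data allow

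*Protocol article*

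**What the plan says.** Section 3.3 sets out two sessions, one per task: "Participants will be asked to complete both sessions in a crossover design". It adds: "In each session, somatosensory processing (attenuation and gating) will be measured pre‐ and post‐task (physical or cognitive". A pre-task reading of each sensory measure therefore exists for every session.

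Section 3.7 states Hypothesis 3 on the change: "The change in somatosensory attenuation (Research Question 3a) and somatosensory gating (Research Question 3b) from pre‐ to post‐task will be predicted by" fatigue change, fatigability, group and task. The model given for both outcomes is "Y_{ijk}=a_{i}+b_{j}+c_{ijk}+d_{ijk}+u_{0i" plus a residual. Its terms are group, task, fatigue change, fatigability and a random intercept. The exploratory reruns in section 3.7.1 add age, time of day and session order, but not the pre-task sensory value.

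The symbol list under the equation disagrees with the hypothesis in one respect and with the design in another. It defines Y as "attenuation or gating at baseline in the" given group, and it describes the random intercept as "capturing group‐level variability".

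For Hypothesis 2, in the same section, the plan does adjust for the starting value: "State fatigue prior to exertion will be included as a covariate in this analysis".

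**The concern.** A raw change score carries all the noise of the pre-task reading. A session that happens to start high will tend to show a fall. A participant-level random intercept cannot remove this, because the noise differs between the two sessions of the same person. The cognitive versus physical contrast is a within-person comparison, so it bears that noise in full.

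A second consequence is possible. If fatigue change is related to the pre-task sensory level, that level feeds both the predictor and, with a minus sign, the outcome. The fatigue-change coefficient could then pick up regression to the mean.

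Research Question 3 asks whether exertion and fatigue alter somatosensory processing, so both coefficients matter to it.

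**Working it through.** **The plan's own figures.** Section 3.8 gives 44 per group for Research Question 1a (effect 0.78, two-sided alpha 0.05, power 95%). A two-sample t-test gives 43.70, so 44 is reproduced. For Research Questions 2 and 3 it says "The sample size gives us power of 90% to detect an effect of 0.70 between two groups at two repeated time points", and 80% at 0.60. A plain two-sample t-test with 44 per group gives 0.901 and 0.795, so these are between-group figures. No power is stated for the task contrast.

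**Variance ratio.** For each person, take the physical-minus-cognitive difference in pre-task value and in post-task value. Assume both differences have variance V, and call their correlation rho.

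- Unadjusted change: variance per person = 2V(1 − rho).
- With the pre-task value as covariate: V(1 − rho²).
- Ratio = (1 − rho²) / [2(1 − rho)] = (1 + rho)/2.

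With two sessions, the person-centred pre-task value is plus or minus half the pre-task difference, so it achieves this same adjustment.

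**Power.** Start from an illustrative 80% unadjusted, two-sided alpha 0.05: power = Φ[(1.96 + 0.8416)/√ratio − 1.96].

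| rho (assumed) | ratio | 2.8016/√ratio − 1.96 | adjusted power |
|---|---|---|---|
| 0.2 | 0.60 | 1.657 | 95% |
| 0.5 | 0.75 | 1.275 | 90% |
| 0.7 | 0.85 | 1.079 | 86% |
| 0.9 | 0.95 | 0.914 | 82% |

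**Simulation of the task contrast.** Set-up: 88 people, two sessions, task effect 0.3, standard errors clustered by participant. The first row has trait SD 0.7 and error SD 0.71; the others have trait SD 0.7, session SD 0.5 and error SD 0.5.

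| Session-to-session fluctuation | implied rho | unadjusted | person-centred covariate |
|---|---|---|---|
| none (stable trait plus error) | 0 | 49% | 78% |
| half reverts by the post-task test | 0.5 × 0.25/0.50 = 0.25 | 63% | 81% |
| persists fully | 0.25/0.50 = 0.5 | 79% | 88% |

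The first row is the most favourable case, because rho is 0 there. The gain shrinks as rho rises.

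**Group contrast.** With a group effect added to the stable-trait set-up, power was 84.4% without the covariate and 84.2% with it. The covariate sums to zero within each person, so this is as expected.

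**Fatigue-change coefficient, no true effect, nominal 5%.** The assumed correlation between pre-task level and fatigue change is 0.4.

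| Scenario | unadjusted | person-centred | raw pre-task value |
|---|---|---|---|
| session fluctuation fully reverts | 33% | 14% | – |
| session fluctuation fully persists | 6% | 9% | – |
| stable trait plus error (trait SD 0.8, error SD 0.6) | 4.9% | 5.7% | 54.9% |

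The covariate lowers false rejection in the first scenario without removing it, and raises it slightly in the second. The raw pre-task value does badly in the third because it is a noisy stand-in for the trait.

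**The case against.** Several points on the other side stand.

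- Change scores answer Research Question 3 directly and are defensible for non-randomised groups. The comparison with Hypothesis 2 is imperfect, because the outcome there is a post-exertion level and not a change.
- A reader might infer that the 80% and 90% in section 3.8 would rise. They would not: those figures are for a between-group effect, which the covariate leaves alone.
- A reader might also infer that the fatigue-change result is biased as planned. The documents do not establish this. It requires session fluctuation that is related to fatigue change and reverts before the post-task test. The apparent support is Hypothesis 2's expectation that baseline sensory values predict post-exertion fatigue, but those terms carry no task index, so as written the relation is between persons. In the stable-trait scenario the unadjusted test is close to nominal (4.9%).
- Taken literally, the symbol list makes Y the baseline value. Until that is corrected, a pre-task covariate would put baseline on both sides of the model.

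The efficiency point survives all of these: for any rho below 1, the unadjusted task contrast has the larger variance.

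**Conclusion.** The point holds as one of efficiency. The Hypothesis 3 equation is written out in full, the pre-task value is available in both sessions, and neither the model nor its reruns use it. The task contrast is therefore less precise than it need be. From an illustrative 80%, the gain is about 15 points at rho 0.2 and about 2 at rho 0.9. This rests on equal pre- and post-task variance, a corrected participant-level model, and a rho the protocol does not give; section 3.7.1 only plans to estimate test–retest reliability.

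For the fatigue-change coefficient, the direction of benefit depends on whether session fluctuation reverts or persists, which is unknown. The documents do not support saying that this coefficient is wrong as planned, or that the analysis is invalid.

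**What to change.** In both Hypothesis 3 models:

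1. Define Y as the pre- to post-task change, in line with the hypothesis, and correct the symbol list throughout.
2. Make the random intercept participant-level.
3. Add one covariate: the session's pre-task attenuation (or gating) minus that participant's mean pre-task value over the two sessions.
4. Do not use the raw pre-task value. With a stable trait measured with error it biases the fatigue-change coefficient, and it would alter the contrast between non-randomised groups that Hypothesis 1 expects to differ in attenuation at baseline.
5. Report the fatigue-change coefficient with and without the covariate, and say that the two can differ in either direction.

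The cost is one degree of freedom per model and one sensitivity analysis, with no new data. The covariate needs both pre-task values, which the exclusions in section 3.5 already largely require for Research Question 3.

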## RESEARCH QUESTIONS

2

Research Question 1: Are pre‐task (baseline) somatosensory attenuation (Research Question 1a) and somatosensory gating (Research Question 1b) different between individuals with long COVID fatigue compared to controls?

Research Question 2: Is state fatigue following exertion predicted by somatosensory attenuation at baseline, somatosensory gating at baseline, the presence of long COVID (long COVID/controls), and the type of task (cognitive/physical), and is performance fatigability a moderator variable in this relation? State fatigue prior to exertion will be included as a covariate in this analysis.

Research Question 3: Is the change in somatosensory attenuation (Research Question 3a) and somatosensory gating (Research Question 3b) from pre‐ to post‐task predicted by the change in state fatigue during exertion, fatigability, the presence of long COVID (long COVID/controls), and the type of task (cognitive/physical)?

Research Question 4: Among individuals with long COVID, is trait fatigue predicted by the increase in state fatigue induced by a physical task, the increase in state fatigue induced by a cognitive task, mood, illness beliefs, autonomic symptoms and autonomic nervous system function?

This study will provide the first comprehensive investigation into the role of somatosensory processing in long COVID fatigue and explore how prominent symptoms in long COVID (autonomic dysfunction, altered mood, beliefs about the meaning of symptoms) interact with somatosensory processing, fatigability and the experience of fatigue.

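### As printed, the Hypothesis 3 model has the pre-task value as its outcome and its only random intercept on group, which contradicts Research Question 3 and leaves two sessions per person unmodelled

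*Protocol article*

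**What the plan says.** Section 2 of the protocol article asks: "Is the change in somatosensory attenuation (Research Question 3a) and somatosensory gating (Research Question 3b) from" before to after the task, predicted by change in state fatigue, fatigability, group and task. The Hypothesis 3 sentence in Section 3.7 names the same outcome.

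The definitions under the Hypothesis 3 equation say something else:

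- `Y_ijk` is "attenuation or gating at baseline in the" given group, task and subject.
- The group effect `a_i` is described as acting ("long COVID vs. control) on baseline attenuation"), and the task effect `b_j` is described in the same way.
- The change in state fatigue, `c_ijk`, is described as "affecting baseline attenuation".
- `u_0i` is a "random intercept for group" `i`. It is the only random effect.

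Section 3.3 has each participant attend both a cognitive and a physical session.

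For Hypothesis 4 the model has one trait-fatigue value per individual. It carries both a residual and a random intercept for the individual, the latter said to capture "variability in trait fatigue not explained by the fixed effects".

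**The concern.** A coefficient from the printed Hypothesis 3 model would describe how a pre-task measurement relates to fatigue that had not yet arisen. That is not the question asked.

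The error structure is a separate fault. The random intercept sits on a two-level factor that is already a fixed effect, while the real clustering, two sessions within a person, has no term.

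Section 3.9 foresees a Stage 2 registered report, so these equations are the pre-specified analysis. Following them literally answers another question. Departing from them leaves the outcome and the unit of clustering to be settled after the data are in.

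**Working it through.** **Inputs.** From the article: 44 participants per group (Section 3.8), two sessions each (Section 3.3), hence 88 participants and 176 person-sessions. The correlation ρ between a participant's two change scores is not given; it is assumed, with a range of 0.1 to 0.7.

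**The plan's own figures.** A two-sample t-test with effect size 0.78, two-sided α 0.05 and 44 per group has power 95.1% (43 per group gives 94.7%), so 44 is reproduced. The 90% and 80% quoted for Research Questions 2 and 3 are matched by a plain two-group t-test at 44 per group (90.1% for 0.70, 79.5% for 0.60). No value of ρ can be read from them.

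**1. Outcome.** Data were simulated with a true slope of 0.40 of change in attenuation on change in fatigue, and pre-task values unrelated to the later change in fatigue (2,000 runs). With the post-minus-pre change as outcome, the mean slope was 0.400. With the pre-task value as outcome it was 0.001. The near-zero value follows from the set-up. Under other set-ups it could differ from zero, but it would still not be the slope that Research Question 3 asks for.

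**2. Group random intercept.** The design matrix for intercept, group and task has rank 3. Adding the two group-intercept columns leaves it at 3, because they already lie in the space of the fixed effects; adding the continuous predictors cannot change that. The contrasts that REML uses carry no information on the group variance (largest entry about 3e-15). With participant intercepts the rank rises to 89 and the variance is estimable.

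What then happens depends on the fit:

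- *Maximum likelihood.* The residuals are orthogonal to the group columns, so a larger group variance only increases the determinant penalty. The estimate goes to zero.
- *REML.* The likelihood is flat in the group variance, so the software stops at an arbitrary value. In one simulated data set (participant and residual variance both 1) the group variance came out at 1.670, with a warning that the Hessian was not positive definite. The group standard error follows from it: √(2 × 1.670 + 0.195²) = √(3.340 + 0.038) = 1.84, where 0.195 is about the standard error without any random effect. With a participant intercept on the same data it was 0.24.

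**3. No participant term and group variance zero.** With two sessions per person, the ratio of true to assumed variance is 1 + ρ for the group contrast and 1 − ρ for the task contrast. The true size of a nominal 5% test is 2 × [1 − Φ(1.96 / √ratio)].

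| ρ (assumed) | √(1+ρ) | Group test, formula | Group test, simulated | Task test, formula | Task test, simulated |
|---|---|---|---|---|---|
| 0.1 | 1.05 | 6.2% | 6.0% | 3.9% | 4.4% |
| 0.3 | 1.14 | 8.6% | 8.2% | 1.9% | 2.1% |
| 0.5 | 1.22 | 11.0% | 10.3% | 0.6% | 0.7% |
| 0.7 | 1.30 | 13.3% | 13.0% | 0.03% | 0.1% |

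The simulations used 5,000 runs per value of ρ. Comparing participant means between groups gave 4.7% to 5.1% throughout.

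**4. Hypothesis 4.** With one value per person, Var(`Y_i`) = σ²_u + σ²_ε, and nothing in the data separates the two. For 44 simulated individuals and six predictors the log-likelihood was −129.6435 whether the random intercept took 0%, 25%, 50%, 75% or 99% of the variance. The fixed-effect estimates are those of ordinary regression in every case.

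**The case against.** The strongest reply is that the intention is plain. The Introduction, Section 2 and the Hypothesis 3 sentence all name the change as outcome. Section 3.5 excludes from Research Question 3 those without post-task measures, which makes sense only for a change outcome. In the Hypothesis 4 model `i` indexes the individual, so `u_0i` in Hypothesis 3 may be a subject intercept carried over with the wrong label.

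Most of this stands as to intent. A reader might infer that the authors plan to analyse baseline values; the documents do not support that. The fault is a contradiction between a hypothesis and its own model. It is still more than a single slip: baseline recurs for `Y_ijk`, `a_i`, `b_j` and `c_ijk` (though not for the fatigability term `d_ijk`), and the intercept is assigned to group in words as well as by index.

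It is also fair to object that the size of the error rests on an unknown ρ. Change scores from different tasks on different days may correlate weakly, and at ρ = 0 there is no distortion. Nor do the two formulas apply directly to change in fatigue and fatigability, which vary both between and within people; their distortion should lie roughly between the two contrasts shown.

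Finally, Research Questions 3 and 4 are not what the study is powered on; that is Research Question 1a, which this point does not touch.

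**Conclusion.** The point holds for the Hypothesis 3 model as printed. Its outcome contradicts the research question, its random intercept cannot be identified beside the fixed group effect, and the pairing of sessions within a participant is not modelled. These conclusions need no assumed figure.

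The size of the resulting error is conditional. If the group intercept is dropped or estimated at zero, the group test runs at about 6% to 13% for ρ from 0.1 to 0.7, and the task test is conservative. If the intercept is fitted and stops at a positive value, the group standard error is arbitrary, and in the example was far too large. A reader might therefore infer that the group test is anti-conservative in any event; that does not follow from the printed model.

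For Hypothesis 4, a reader might infer that the model cannot be used at all. Only the split of variance between random intercept and residual is lost; the coefficients that the hypothesis concerns are unaffected. Several trait-fatigue scales are collected (Section 3.4.1), but the equation has no index for scale, so they do not make the term estimable. This is a minor point.

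**What to change.** In Section 3.7, Hypothesis 3:

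- define `Y_ijk` as post-task minus pre-task attenuation (or gating, in its own model) in session `j`;
- remove the references to baseline from the definitions of `a_i`, `b_j` and `c_ijk`;
- replace `u_0i` by a participant random intercept, `u_0k`.

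In Hypothesis 4, delete `u_0i` and call the model multiple linear regression.

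Adding the pre-task value as a covariate is not part of this correction. The groups are not randomised and Hypothesis 1 expects them to differ at baseline, so adjustment would change what the group coefficient means and would need its own justification.

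The cost is the wording of two model descriptions. No new data are needed and the sample size does not change.
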